## Abstract

**Background::**

There is no safe level of exposure to second hand tobacco smoke (SHS). The World Health Organization has stressed that 100% smoke-free environments are the only effective way to protect the population from the harmful effects of exposure to SHS.

**Design::**

A multiphase study with a descriptive cross-sectional questionnaire phase 1 and a phase 2 cluster randomized controlled trial (RCT), conceptualized to determine the effectiveness of a school-based ‘tobacco free’ health education intervention on adolescents’ knowledge and attitude towards SHS.

**Methods::**

Baseline assessment will include a questionnaire followed by estimation of salivary cotinine levels. The experimental arm will receive the ‘tobacco free’ intervention, which includes 40 min health education session delivered once a week for 3 consecutive weeks. Participants will also be given ‘take home brochures’ every week containing messages on the effects of tobacco and how to make their homes smoke-free. The sample of 250 participants, for the Phase 2 RCT, with salivary cotinine levels of > 0.1 ng/mL will be selected from the participants of the Phase 1 study. The effect of the intervention will be quantitatively assessed by estimating the salivary cotinine levels after the intervention. Participants in the control arm will receive conventional standard health education once.

**Conclusion::**

This research will help in assessing if there is any change in the salivary cotinine levels and the knowledge, attitude and behaviour scores after the health educational intervention and help in developing an effective school-based ‘tobacco free’ intervention program which could be incorporated into the school curriculum. This study has received the Public Health Research Initiative (PHRI) Research Grant of Rs. 18,99,205 and is registered with the Clinical Trial Registry of India (CTRI) with number CTRI/2018/09/015706 (Registered on 13/09/2018). Ethical approval has been obtained from The Institutional Ethics Committee (No.17021 dated 13 march 2017).

## Introduction

“*Tobacco is the single most preventable cause of death in the world today. During the 21st century, it is estimated to kill one billion*”(WHO, 2008). Cigarettes are found to contain about 1.5% nicotine by weight, which produces 1–2 mg of bioavailable nicotine per cigarette. Therefore, inhaling tobacco smoke is the main source of nicotine exposure for the general population (CDC, 2018). 

Cotinine, a major metabolite of Nicotine is a useful biomarker with a half life of about 16 hours and can be used to distinguish tobacco users from non- users (Raja et al., 2016).

Although many countries of the World have passed laws making workplaces, public places, and restaurants smoke-free, still millions of children and adults continue to breathe second hand tobacco smoke (SHS) (CDC, 2017). According to the World Health Organization (2018), the health of almost half of the world’s children is affected by exposure to environmental tobacco smoke (ETS).

SHS exposure has been linked to a variety of serious diseases in adults as well as in children, such as coronary heart disease, lung cancer, breast cancer, respiratory symptoms and illnesses, otitis media and during pregnancy causes pre-term low birth weight deliveries (WHO., 2018).

There is no safe level of exposure to second hand smoke. Even brief exposures can be harmful. Moreover, studies (Farkas et al., 2000; Öberg et al ., 2011) have even shown that “*children exposed to SHS are more likely to become smokers themselves when they grow older compared to those unexposed*”.

This paper describes the study protocol for a multi-phase study, which has been conceptualized to develop and evaluate a ‘*tobacco free*’ intervention program to reduce children’s exposure to Second Hand Tobacco Smoke. 

*Rationale*

Although educating children might be an effective method of reducing tobacco prevalence not only among the present adults but also among the adolescents who are our future adults (Alwan et al., 2010; Siddiqi et al., 2010; Zafar Ullah et al., 2013; Eakin et al., 2014; Loke and Mak, 2015), literature search revealed gaps in research pertaining to tobacco free intervention among adolescents, resulting in the conception of this study. 

**Figure 1 F1:**
[figure not shown]
Flow of Participants in Phase 1

**Figure 2 F2:**
[figure not shown]
Flow of Participants in Phase 2

## Materials and Methods

*Study setting*

The study will be conducted among 12 year old school children of Mangalore, India. 

*Broad objective:*

To contribute toward national efforts to protect children from harmful effects of SHS, the objective of this study is to develop effective school-based intervention to reduce exposure and improve adolescents’ knowledge and attitude towards Second Hand tobacco Smoke and to promote smoke free homes.

*Specific objectives*

To assess exposure to second hand tobacco smoke among 12 year old school children.

To carry out a school based ‘*tobacco free*’ educational intervention program among 12 year old school children.

To assess the Salivary Cotinine level as well as the knowledge, attitude and avoidance behaviour towards second hand tobacco smoke among 12 year old school children, before and after carrying out an intervention. 

*Study design and registration*

This will be a multiphase study using multiphase sampling technique among adolescents in Mangalore, India. The first phase will be a descriptive cross-sectional study. A cluster random sampling of all the schools in Mangalore will be done to obtain the required sample size of 1400. A questionnaire will then be administered to the 12 year olds in the selected schools, who fulfil the inclusion criteria. Data will be analysed and those students who report exposure to second hand tobacco smoke will be selected and their salivary cotinine level checked until we get a sample of 250 subjects with salivary cotinine levels of > 0.1 ng/mL (Avila-Tang et al., 2012). These will form the sample for the second phase of the study which will be a randomized controlled trial. (Figures 1 and 2). 

The protocol follows SPIRIT guidelines (Chan et al., 2013) and includes all items from the World Health Organization Trial Registration Data Set (WHO., 2019) [Appendix 1]. The trial has been registered with the Clinical Trial Registry of India (CTRI) with number CTRI/2018/09/015706 (Registered on 13/09/2018).

*Sample size calculation*

*For phase 1: (Cross-sectional study)*

The sample size estimation was done using the formula:

$n=\frac{{\left(Z_{1-a/2}\right)}^{2}\mathrm{PQ}}{d^{2}}$

where: 

Z_1-α/2_ = 1.96 (when α is 5% at 95% confidence limits)

P= Proportion of the event in the population (29%) (Singh et al., 2011)

Q=1-P (0.71)

d= Acceptable margin of error (3%)

With a design effect at 1.5 and a non-response at 5%, the final sample size was calculated to be 1400 for the Phase 1 study.

*For phase 2: (Randomized controlled trial)*

The sample size calculation for Phase 2 randomized controlled trial was done using G Power 3.1.2. We calculated a total sample size of 250 with125 in the control group and 125 in the intervention group, 90% power, an Effect size of 0.3, confidence interval at 95% and attrition at 10%.

*Recruitment and eligibility*

The study is now recruiting and the criteria for eligibility are as follows, 

*Inclusion criteria for phase 1 study *

1. All Schools in Mangalore who have primary and secondary schools in the same campus.

2. Those schools who consent to participate in the study

3. Students whose parents give written informed consent and they themselves give informed assent.

*Exclusion criteria for phase 1 study*

1. Participants who are self-reported smokers.

*Inclusion criteria for phase 2 study *

1. Inclusion criteria: Participants with salivary cotinine levels of > 0.1 ng/mL

2. Exclusion criteria: Participants whose sibling is already a participant in the study

*Study procedure*

*Phase 1*

The first phase will be a descriptive cross-sectional study. A cluster random sampling of all the schools in Mangalore will be done to obtain the required sample size of 1,400. A questionnaire will then be administered to the 12 year olds in the selected schools, who fulfil the inclusion criteria. 

*Questionnaire*

Demographic data will be recorded. Socioeconomic status will be assessed using the BG Prasad Scale (Prasad., 1961) modified considering the base of Consumer Price Index (CPI) for 2017 (Singh et al., 2017). The questionnaire will have two components, one to assess children’s exposure to SHS using Questionnaire 1 which has 5 questions (Lin et al., 2010). The second component, Questionnaire 2, is a 25 item questionnaire (Gharaibeh et al., 2011) to determine Children’s knowledge, attitude and behaviour towards second hand smoke. Knowledge will be assessed using 10 items, Attitude with 5 items, Avoidance behaviour towards second hand smoke will be assessed using 5 items and Self-efficacy of avoidance will be assessed using 5 items. This assessment will be carried out at the start of Phase 1 and at all 3 follow-up time points in Phase 2.

The questionnaire will be administered to 10 individuals and reliability measured using the Cronbach’s coefficient alpha. A high coefficient indicates that the items are consistently measuring the same underlying construct.

Data will be analysed and those students who report exposure to second hand tobacco smoke will be selected and their salivary cotinine level checked.

*Salivary Cotinine level estimation*

Children’s exposure to SHS will be determined by measuring their salivary cotinine levels twice, one at the end of Phase 1(baseline) and second at the 3rd follow-up, i.e., at 12 months after the intervention. Salivary cotinine is a sensitive biochemical marker which is strongly associated with exposure to SHS. It has a half-life of 16 hours and is a widely recognized marker for detecting both active and passive smoking. 

Saliva collection: Saliva will be collected not before at least 60 minutes after a major meal. Participant will be asked to rinse mouth thoroughly with water 10 minutes before sample is collected. The head is tilted forward, allowing the saliva to pool on the floor of the mouth. Whole saliva will be collected in a labelled vial by unstimulated passive drool. After collection, sample will be refrigerated within 30 minutes, and frozen at or below -20ºC within 4 hours of collection. 

Salimetrics^®^ High Sensitivity Salivary Cotinine Quantitative Enzyme Immunoassay Kit will be used for cotinine estimation in saliva (Salimetrics., 2018). There will not be any personal identifiers on the vials sent to the laboratory and individual results will not be disclosed.

The participants who have salivary cotinine levels of > 0.1 ng/mL will be selected and they will form the sampling frame for the second phase of the study which will be a randomized controlled trial.

*Phase 2*

This phase will be a randomized controlled trial, with a sample size of 250, 125 participants in the intervention group and 125 in the control group.

Random allocation: Sequence generation will be done using the table of random numbers. We will adopt the process of first identifying potential individual participants in each cluster, recruiting these participants and then do cluster randomisation. Allocation concealment will be done using sequentially numbered, opaque, sealed envelopes (SNOSE). The study will be outcome assessor blinded.

*Intervention*

The intervention consists of 40 min ‘tobacco free’ health education session delivered once a week for 3 consecutive weeks by the principal investigator (PI) (AR). The first session will address tobacco and its adverse effects. The second session will be on laws regarding tobacco in India and the World and the third session will be on how to prevent exposure to tobacco. Teaching methods include lectures, demonstrations, discussions, storytelling and quiz. Children are also given take home brochures every week that contains messages on the effects of tobacco and how to make their homes smoke-free.

There will be 3 follow up time points. The first follow up will be at the 3rd month, second follow up at the 6th month and the third follow up at 12 months after the intervention. On the first day of each follow up, the PI will reinforce the key points of the intervention and also discuss with the students regarding their experiences at home and the challenges they faced. The timeline is given in Appendix 2. Participants in the control arm will receive conventional standard health education once, whereas those who report tobacco use will be encouraged to participate in tobacco counselling.

*Study outcomes*

To assess if there is any change in the salivary cotinine levels and the knowledge, attitude and behaviour scores of the participants after a ‘tobacco free’ health educational intervention.

To develop effective school-based intervention to reduce exposure and improve adolescents’ knowledge and attitude towards Second Hand tobacco Smoke and to promote smoke free homes.

*Data analysis plan*

Analysis will be done based on both the Intention to Treat and Per Protocol analysis. The data will be entered into the SPSS software (IBM Corp. Released 2011. IBM SPSS Statistics for Windows, Version 20.0. Armonk, NY: IBM Corp.) and analysed. Descriptive statistics will be presented and sub group analysis will be done wherever needed. The level of significance will be kept at 0.05 with 95% confidence levels. For the phase 1 study, Chi square test will be done for categorical variables and Independent sample t test will be done to compare means. Logistic regression will be done to obtain the adjusted odds ratio. For the phase 2 study, Paired sample t - test will be done.

*Ethical aspects*

Ethical approval has been obtained from The Institutional Ethics Committee (No.17021 dated 13 march 2017). Written informed consent from parents and informed assent from the participants will be obtained by the principal investigator prior to recruitment. Confidentiality of the participants will be maintained at all times. The saliva collected will be completely utilized for laboratory evaluation and no biological specimen will be stored for further use.

In conclusions, although children might be exposed to SHS in a lot of places, the primary source of SHS exposure is in their homes (Zafar Ullah., 2013; WHO., 2015). As the prevalence of adult smokers increases, so does the number of children who breathe air polluted by tobacco smoke, particularly at home. This will be a first of its kind study to be done in this part of the World. The World Health Organization has stressed on the need for “*implementing complete smoke-free environments as the only effective way to protect the population from the harmful effects of exposure to SHS*” (WHO., 2015). Educating children about the ill effects of second hand smoke will empower them to decide and take action so as to choose to breathe in an atmosphere unadulterated with toxic chemicals released from tobacco smoke. The child might also take home and share this message thus helping in reducing tobacco use not only among the present adults but also among the adolescents who are our future adults. India is a signatory to the “*WHO Framework Convention on Tobacco Control (FCTC), which calls for measures to protect people from SHS*” (WHO., 2019). The outcome of this research will help in developing effective school-based intervention to improve adolescents’ knowledge and attitude towards Second Hand Smoke and to promote smoke free homes.

*Funding *

This study has received the Public Health Research Initiative (PHRI) Research Grant of Rs. 18,99,205 as an extramural fund set up by Public Health foundation of India (PHFI) in collaboration with Science and Engineering Research Board (SERB, A Statutory Body under Department of Science and Technology (DST), Government of India). The funding agency has not influenced the design of this study and will not influence its execution, analyses, interpretation of the data. 

*Authors’ contributions*

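### The Phase 2 power of 90% at effect size 0.3 fits a within-arm paired t-test, not the randomised comparison between arms; if 0.3 is a between-arm standardised difference, power is about 66%, or 61% after the stated attrition, before clustering

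*Protocol article*

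**What the plan says.** The sample size section of the protocol article (Materials and Methods, Phase 2) reports a G Power calculation: "The sample size calculation for Phase 2 randomized controlled trial was done using G Power 3.1.2". The result is a "total sample size of 250 with125 in the control group and 125 in the intervention group, 90% power, an Effect size of 0.3", with "confidence interval at 95% and attrition at 10" per cent. The study procedure for Phase 2 repeats the numbers: "with a sample size of 250, 125 participants in the intervention group and 125 in the control group".

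The section does not say which G Power test was used, which outcome the effect size belongs to, or which metric it is in. The data analysis plan fixes alpha ("The level of significance will be kept at 0.05 with 95% confidence levels") and names one test for Phase 2, the paired sample t-test. The abstract describes Phase 2 as a cluster randomised trial of the effectiveness of the intervention, and the random allocation paragraph says that clusters are randomised. A design effect (1.5) is given for Phase 1 only.

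**The concern.** A trial that randomises schools to an intervention or to conventional health education, in order to judge effectiveness, answers its question by comparing the arms. Its power statement should refer to that comparison. With 125 per arm, a standardised difference of 0.3 is well short of 90% power in a two-group test, so the stated figure appears to belong to a different test.

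A paired t-test within an arm asks whether that arm changed from baseline. Children's knowledge scores or cotinine can change over 12 months in either arm. A significant change in one arm and not in the other is not evidence of an intervention effect. If 0.3 is the between-arm effect of interest, readers are told that the chance of missing it is 10%, when for an unadjusted comparison after attrition it would be about 39% (100% − 61%). A null result could then be read as stronger evidence against the programme than it is.

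**Working it through.** **Inputs from the protocol article.** 125 per arm; power 90%; effect size 0.3; alpha 0.05; attrition 10%, leaving 125 × 0.9 = 112.5 per arm.

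**Assumptions.** Two-sided testing (sidedness is not stated). The metric of 0.3 is varied below. Powers are from the noncentral t distribution.

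**1. Reproducing the 90%: paired t-test within one arm, dz = 0.3.** The noncentrality parameter is dz × √n, on n − 1 degrees of freedom.
- n = 125: 0.3 × √125 = 3.354, power 91.4%.
- n = 112.5: 0.3 × √112.5 = 3.182, power 88.4%.
- Pairs needed for 90%: 119. With 10% attrition, 119 / 0.9 = 132.2, so 132 to 133 per arm.

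This comes within two points of the stated power before and after attrition. It does not return 125 per arm exactly.

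**2. Comparison of the two arms, d = 0.3.** The noncentrality parameter is d × √(n/2), on 2n − 2 degrees of freedom.
- n = 125: 0.3 × √62.5 = 2.372, power 65.6%.
- n = 112.5: 0.3 × √56.25 = 2.250, power 61.0%.
- One-sided at 5%: 76.4% and 72.5%.
- Needed for 90%, two-sided: the normal approximation is n = 2 × (1.960 + 1.282)² / 0.3² ≈ 233.5 per arm; the t-test needs 235, or 470 in total. With attrition, 470 / 0.9 = 522.2, so 523.
- Difference detectable with 90% power, (1.960 + 1.282) × √(2/n): 0.41 SD at n = 125 and 0.43 SD at n = 112.5.

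**3. Other G Power readings of 0.3.**

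| Reading | Total for 90% | With 10% attrition |
|---|---|---|
| Cohen's f = 0.3, two-group ANOVA | 119 | 133 |
| Chi-square w = 0.3, 1 df | 117 | 130 |
| Two-sample t, d = 0.3 | 470 | 523 |
| Paired t, dz = 0.3, in each of two arms | 238 | 265 |

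None of these gives 250 with 10% attrition. With two equal groups f = d/2, so f = 0.3 means d = 0.6; 112.5 per arm then gives about 99% before clustering.

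**4. Clustering on the d = 0.3 reading.** Phase 2 states no intracluster correlation, cluster size or design effect. If the Phase 1 value of 1.5 applied (assumption), the effective number per arm after attrition is 112.5 / 1.5 = 75. The noncentrality parameter is 0.3 × √37.5 = 1.837 and power is about 45%. Over an illustrative range of 10 to 30 children per cluster and intracluster correlations of 0.01 to 0.05, power after attrition runs from about 58% down to 30% (normal approximation).

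**5. Baseline adjustment on the d = 0.3 reading, before clustering.** The effective number per arm is 112.5 / (1 − r²), where r is the correlation between baseline and follow-up (assumed; none is stated).
- r = 0.5: 150.0 per arm, power about 74%.
- r = 0.6: 175.8 per arm, power about 80%.
- r = 0.7: 220.6 per arm, power about 88%.

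Reaching 90% after attrition would need r of about 0.72.

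**The case against.** A reader might infer that the 90% is simply an arithmetic error, or that the trial is shown to be underpowered. The article supports neither. It says only "an Effect size of 0.3". The 66% and 61% require that to be Cohen's d between arms, which is an assumption. The paired t-test, the only Phase 2 test named, roughly reproduces the stated power. If 0.3 were Cohen's f, the trial would have about 99% power before clustering and would still be near 90% at a design effect of 1.9. A condensed article may also leave the test, outcome and metric to a fuller document, so their absence is not in itself a defect. Nor can one say that no method gives 250, because only a limited set of readings was tried. The 39% chance of missing the effect is for an unadjusted analysis, and baseline adjustment could reduce it considerably.

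All of this stands and limits the claim. It does not rescue the power statement. The reading closest to 90% is a within-arm test that does not address the question the trial randomises to answer, and even that reading needs 132 to 133 per arm with the stated attrition. The f reading makes the trial larger than its inputs require, so it does not explain 250 either. One-sided testing does not bring the between-arm comparison to 90%.

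**Conclusion.** The point holds as a mismatch between the power statement and the randomised comparison. The stated 90% with 125 per arm fits a paired test within one arm. For the comparison of arms, the figure depends on a metric that the article does not give. On the most direct reading (Cohen's d of 0.3, two-sided 5%, unadjusted), power is about 66%, or 61% after the stated attrition, and lower with clustering, by an amount the article does not allow one to fix (about 45% under the assumed design effect of 1.5). On the Cohen's f reading power would be ample before clustering, but the inputs would not lead to 250. In each case the stated power, effect size, attrition and sample size do not fit together for the comparison between arms. The figure should be corrected because readers will rely on it when they interpret the result.

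**What to change.** Keep 250 and restate the power for the between-arm comparison, naming the outcome, the test and the effect-size metric. If 0.3 is a standardised difference between arms, the statement would be about 61% power for 0.3, or 90% power for about 0.43 SD, after 10% attrition and before clustering. The Phase 2 design effect should then be applied, with its assumed intracluster correlation and cluster size given. At a design effect of 1.5, for example, the difference detectable with 90% power rises to 0.43 × √1.5 ≈ 0.53 SD.

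If a baseline-adjusted comparison of the arms is adopted in place of the paired t-test, report its power with the assumed correlation stated: about 74%, 80% or 88% for r = 0.5, 0.6 or 0.7, again before clustering. If 0.3 was meant as another metric, say so and show how 250 follows from it.

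The cost is wording only. No participants are added. On the d reading the stated power becomes less favourable.

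### The scores are measured on four occasions, but the only Phase 2 test named takes two occasions within one arm, and no lead time point or between-arm contrast is fixed for them

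*Protocol article*

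**What the plan says.** All references are to the protocol article, Materials and Methods.

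- Questionnaire: "This assessment will be carried out at the start of Phase 1 and at all 3 follow-up time points in Phase 2". There are four domains: "Knowledge will be assessed using 10 items, Attitude with 5 items, Avoidance behaviour towards second hand smoke will be assessed using 5 items", plus five self-efficacy items.
- Intervention (follow-up timing, counted from the intervention): "The first follow up will be at the 3rd month, second follow up at the 6th month and the third follow up at 12 months".
- Study outcomes: "To assess if there is any change in the salivary cotinine levels and the knowledge, attitude and behaviour scores of the participants". No time point is singled out.
- Salivary Cotinine level estimation: the biomarker follows a different schedule, "measuring their salivary cotinine levels twice, one at the end of Phase 1(baseline) and second at the 3rd follow-up", the latter at 12 months.
- Data analysis plan: "For the phase 2 study, Paired sample t - test will be done", and "The level of significance will be kept at 0.05 with 95% confidence levels". No other Phase 2 method and no rule for multiple tests is given.
- Random allocation: schools are randomised as clusters.

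**The concern.** A paired t-test takes two measurements per child. That matches the number of cotinine occasions (two) but not the number of score occasions (four). Because the article names the test and also sets the schedule, this is a mismatch between two things it fixes, not a detail left for a later document.

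Two ways of applying the test fit the text:

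1. Compare baseline with one follow-up. The other two questionnaires then add nothing to inference.
2. Compare baseline with each follow-up in turn. This gives several tests per score at an unadjusted 0.05, with no rule for combining them.

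Neither gives one estimate of how the arms differ over the year, and neither uses the fact that each child supplies three correlated post-intervention scores. Part of this is the wider fault that a within-arm test does not compare the arms. A separate part would survive that repair: a two-sample or cluster-adjusted comparison at 12 months alone would still leave the 3- and 6-month scores out.

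**Working it through.** **The plan's own figure.** The Sample size calculation reads "We calculated a total sample size of 250 with125 in the control group and 125 in the intervention group, 90% power", with effect size 0.3 and 10% attrition. The type of effect size and the sidedness are not stated. Taken as two-sided:

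- Two-sample comparison, d = 0.3: 235 per arm, or 262 after attrition. This does not match.
- Paired test within one arm, standardised change 0.3: 119 per arm, or 133 after attrition. This is nearer but not exact. Power is 0.914 with 125 children and 0.882 with 112.

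The 250 is therefore not reproduced. No variant tried with four occasions gives it either. The point does not depend on this figure.

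**Route 2: number of tests.** The stated objective is assessment before and after the intervention, so the relevant pairs are baseline against each follow-up: 3 per score and arm. With four domains this is 3 × 4 = 12 per arm and 24 over two arms (18 if self-efficacy is left out).

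Chance of at least one false positive at 0.05:

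- One score, one arm, three independent tests: 1 − 0.95³ = 0.143. With the shared baseline (correlation 0.5 between changes), simulation gives about 0.12.
- 12 tests: 1 − 0.95¹² = 0.46. 24 tests: 1 − 0.95²⁴ = 0.71. Both assume independence, so they are upper guides.

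**Precision available from all three follow-ups.** Inputs: 125 × 0.9 = 112.5, so 112 completers per arm (document). Assumed: a difference of 0.3 SD, the same at 3, 6 and 12 months; equal correlation r between follow-ups after baseline adjustment; two-sided 0.05.

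Variance of the three-visit mean relative to one visit = (1 + 2r)/3. Effective standardised difference = 0.3/√ratio.

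| r | variance ratio | effective d | power, 112 per arm |
|---|---|---|---|
| one visit | 1 | 0.300 | 0.608 |
| 0.3 | 0.533 | 0.411 | 0.865 |
| 0.5 | 0.667 | 0.367 | 0.782 |
| 0.7 | 0.800 | 0.335 | 0.705 |

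**With clustering.** Assumed: 8 schools per arm, 14 children each, ICC 0.02, t with 14 df, school-level variance not reduced by averaging. Variance of the arm difference = (2/8) × [0.02 + 0.98 × ratio/14].

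- One visit: 0.25 × (0.02 + 0.07) = 0.0225, noncentrality 0.3/0.15 = 2.0, power 0.46.
- r = 0.3, 0.5, 0.7: power 0.64, 0.58, 0.53.

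The gains are 0.18, 0.12 and 0.07, against 0.26, 0.17 and 0.10 without clustering.

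**When the effect is not constant.** Suppose the 12-month effect is 0.3 SD but the three-visit average is 0.2 SD. The effective d for the average is 0.2/√ratio = 0.274, 0.245, 0.224, and its power is 0.53, 0.45, 0.38. All are below the 0.608 for 12 months alone. In this unclustered setting the average gains only if it exceeds 0.3 × √ratio, that is 0.22, 0.24 or 0.27 SD for r = 0.3, 0.5, 0.7.

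**The case against.** Several arguments on the other side have force.

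- **Extra tests are not a stated fact.** A reader might infer that the plan will run the paired test at every visit and so inflate false positives. The article does not say so. It also promises descriptive statistics, so the 3- and 6-month scores may simply be described. The 12- and 24-test figures apply only if the second route is taken.
- **Six pairs per score is too many.** Four occasions form six pairs, but three of those compare one follow-up with another and serve no stated objective. Three is the right count.
- **The 61% is not the power of the planned test.** The within-arm paired test has about 0.88 power at a standardised change of 0.3 with 112 children. The 61% belongs to a between-arm comparison that the plan does not contain, so the precision gain exists only once that comparison is introduced.
- **A constant effect is doubtful here.** The Intervention section has the investigator reinforce the key messages at each follow-up, so the effect could grow or fade between visits. The average also answers a different question from the 12-month effect.
- **A single main time point is legitimate.** Cotinine is measured only at baseline and 12 months, so a 12-month lead contrast would align the scores with the biomarker. The interim visits also deliver reinforcement and show the time course, so precision is not their only purpose.

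All of this limits the size of the point and leaves the choice of lead contrast open. None of it removes the mismatch: the named test does not settle how four occasions are used, and no lead time point is fixed for the scores.

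**Conclusion.** The point holds in a limited form. The article fixes four occasions for the scores and names one two-occasion, within-arm test for Phase 2. Two follow-ups are therefore either unused in inference or tested separately at 0.05, and either way there is no between-arm estimate using all of them.

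The benefit of repair is conditional. It takes a between-arm analysis as given, a constant 0.3 SD effect, and correlations of 0.3 to 0.7, none of which the article supplies. On those terms, averaging three visits cuts the variance to 0.53 to 0.80 of a single visit's and lifts power from 0.61 to between 0.87 and 0.71 before clustering. It gains less with clustering and can lose power if the earlier effects are smaller. A reader might conclude that the year average must be the lead contrast; the document does not support that. The change should be made, since it recovers information already being collected, but the larger fault in the same sentence remains the absence of a comparison between arms.

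**What to change.** For the scores, replace the paired t-test with one longitudinal mixed model per score: arm, visit, arm-by-visit and baseline score as fixed effects, with random effects for school and child. Name one lead between-arm contrast before the data are examined:

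- the 12-month difference, which aligns with cotinine; or
- the average difference over 3, 6 and 12 months, which is more precise if the effect is roughly constant.

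Report the visit-specific differences from the same model, so that waning or growth is visible. State that the contrasts other than the lead one are supportive.

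The cost is wording in the analysis plan and slightly more complex modelling; no extra data are needed. If the average is chosen, it must be read together with the 12-month estimate, which the same model provides.
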